## Abstract

**Background:**

Fecal occult blood testing has been offered for many years in the German health care system, but participation rates have been notoriously low.

**Objective:**

The aim of this study is to evaluate the effect of various personal invitation schemes on the use of fecal immunochemical tests (FITs) in persons aged 50-54 years.

**Methods:**

This study consists of a three-armed randomized controlled trial: (1) arm A: an invitation letter from a health insurance plan including a FIT test kit, (2) arm B: an invitation letter from a health insurance plan including an offer to receive a free FIT test kit by mail upon easy-to-handle request (ie, by internet, fax, or reply mail), and (3) arm C: an information letter on an existing colonoscopy offer (ie, control). Within arms A and B, a random selection of 50% of the study population will receive reminder letters, the effects of which are to be evaluated in a substudy.

**Results:**

A total of 17,532 persons aged 50-54 years in a statutory health insurance plan in the southwest of Germany—AOK Baden-Wuerttemberg—were sent an initial invitation, and 5825 reminder letters were sent out. The primary end point is FIT usage within 1 year from receipt of invitation or information letter. The main secondary end points include gender-specific FIT usage within 1 year, rates of positive test results, rates of colonoscopies following a positive test result, and detection rates of advanced neoplasms. The study was launched in September 2017. Data collection and workup were completed in fall 2019.

**Conclusions:**

This randomized controlled trial will provide important empirical evidence for enhancing colorectal cancer screening offers in the German health care system.

**Trial Registration:**

German Clinical Trials Register (DRKS) DRKS00011858; https://bit.ly/2UBTIdt

**International Registered Report Identifier (IRRID):**

DERR1-10.2196/16413

## Introduction

### Background

Annual or biennial screening by fecal occult blood tests (FOBTs) has been shown by randomized clinical trials to reduce colorectal cancer (CRC) mortality by up to 30% [1]. These effects were achieved even with guaiac-based FOBTs (gFOBTs), which had limited sensitivity in detecting CRC and its precursors. Even stronger effects are to be expected by screening with immunochemical FOBTs (iFOBTs), often called fecal immunochemical tests (FITs), which have substantially higher sensitivity than gFOBTs [2]. FITs are now commonly recommended for CRC screening by national and international guidelines [2-4], and are increasingly offered for CRC screening in many countries [5,6]. However, participation rates in screening have remained low in countries where screening is offered in an opportunistic manner without targeted invitation of the eligible population [5]. This particularly applies to Germany, where gFOBT screening had been offered from 1977 to March 2017; FIT-based screening has been offered from age 50 years on since April 2017. For conducting FITs that are covered by the health insurance system, people have to pick up and return the tests at medical practices. Although personal information letters on CRC screening offers have been sent to the eligible population since July 2019 [3], they do not include FITs or specific low-threshold access to FITs, which are deemed to be crucial to achieve high participation rates [7,8]. The aim of this trial is to assess the effect of various invitation schemes on use of FITs for CRC screening in routine practice in the German health care system.

### Objectives

The primary outcome that will be investigated is as follows: determine the proportion of people completing a FIT within 1 year after receiving a personal invitation letter within each trial arm.

Secondary outcomes are to determine the following:

The rate of positive test results.The rate of performing a colonoscopy after a positive test.The rate of performing a colonoscopy after a negative test.The rate of discovered advanced colorectal neoplasia (ie, advanced adenomas and cancer).The positive predictive value of the test.The rate of performing a screening colonoscopy, in general, within 1 year.

Gender-specific analyses will be conducted.

## Methods

### Setting and Design

This protocol follows the Standard Protocol Items: Recommendations for Interventional Trials (SPIRIT) 2013 Statement for clinical trial protocols [9] and the Fecal Immunochemical TesTs for Hemoglobin Evaluation Reporting (FITTER) guidelines [10].

The study is being conducted by the German Cancer Research Center (DKFZ) in cooperation with a statutory health insurance plan in the southwest of Germany: AOK Baden-Wuerttemberg (AOK BW).

The study is designed as a three-armed randomized controlled trial, in which 17,532 people aged 50-54 years are randomly selected to receive a letter from their health insurance plan (ie, AOK BW) with the following: (1) arm A: an invitation letter including a FIT test kit, (2) arm B: an invitation letter including an offer to receive a free FIT test kit by mail upon easy-to-handle request (ie, via Internet, fax, or reply mail), or (3) arm C: an information letter on CRC screening in the form of a colonoscopy; the control group represents routine practice with no study-related adaption of the letter. There are about 5844 insurants per arm. In addition, a reminder letter is being sent by random selection to 50% of the population in arms A and B. Prior to the recruitment of participants, the study, which was launched in 2017, was approved by the ethics committee of the Medical Faculty of the University of Heidelberg, Germany. It was registered in the German Clinical Trials Register (DRKS) on March 20, 2017 (DRKS-ID: DRKS00011858) with the following title: *Increase of the usage and effectiveness of colorectal cancer screening by means of targeted invitations with and without providing fecal immunochemical tests*. Written informed consent is being obtained from all participants.

Regardless of the FITs offered to participants in arms A and B within the intervention groups, the entire targeted population has access to CRC screening offers in routine practice according to law. However, only the opportunistic screening program is available at the time of study recruitment: CRC screening comprises annual testing for blood in the stool using the FIT or by performing a screening colonoscopy from age 50 years for men and women within a specific health insurance plan of AOK BW called *AOK-FacharztProgramm* (AOK Specialist Program); screening colonoscopy is otherwise offered from age 55 years in Germany during the recruitment period.

The study consists of two parts: (1) the mailing of different personal invitation letters for CRC screening, with low-threshold access to a FIT in the intervention arms, and (2) the follow-up of the use and outcome of a colonoscopy after a positive FIT, as well as the assessment of conducted FITs and colonoscopies in routine practice within 1 year after the initial invitation. Routine FIT and colonoscopy usage is derived from AOK BW claims data, which is being aggregated and pseudonymized where consent was obtained. All collected information is being stored and monitored in a study database by trained staff. The study design and the study assessments are shown in Figure 1 and Table 1, respectively.

**Figure 1 figure1:**
[figure not shown]
Study design. Total expected fecal immunochemical test (FIT) use per study arm: A=35%, B=17.5%, and C=10%. Participants in arms A and B may receive a FIT as part of the intervention or can additionally request it in routine practice. Participants in arm C (ie, control) can only use the FIT in routine practice. Data on the use of screening methods until 1 year after the initial invitation will be collected. AOK BW: AOK Baden-Wuerttemberg; A1 and A2: subgroups of arm A; and B1 and B2: subgroups of arm B.

**Table 1 table1:** Overview of study assessments at relevant time points.

Assessments		T0 (0 wk)	T1								T2 (6 months after positive FIT^a^)	T3 (1 year)
			2 wk	4 wk	6 wk	8 wk	10 wk	12 wk	14 wk	>14^b^ wk		
**Randomization and initial invitations**												
	Randomization^c^	✓	–^d^	–	–	–	–	–	–	–	–	–
	Subrandomization^e^	✓	–	–	–	–	–	–	–	–	–	–
	Tranche 1	✓	–	–	–	–	–	–	–	–	–	–
	Reminder 1	–	–	✓	–	–	–	–	–	–	–	–
	Tranche 2	–	✓	–	–	–	–	–	–	–	–	–
	Reminder 2	–	–	–	✓	–	–	–	–	–	–	–
	Tranche 3	–	–	✓	–	–	–	–	–	–	–	–
	Reminder 3	–	–	–	–	✓	–	–	–	–	–	–
	Tranche 4	–	–	–	✓	–	–	–	–	–	–	–
	Reminder 4	–	–	–	–	–	✓	–	–	–	–	–
	Tranche 5	–	–	–	–	✓	–	–	–	–	–	–
	Reminder 5	–	–	–	–	–	–	✓	–	–	–	–
	Tranche 6	–	–	–	–	–	✓	–	–	–	–	–
	Reminder 6	–	–	–	–	–	–	–	✓	–	–	–
**Laboratory analysis of the provided FITs and notification about results**												
	Laboratory analysis	–	✓	✓	✓	✓	✓	✓	✓	✓	–	–
	Notification	–	✓	✓	✓	✓	✓	✓	✓	✓	–	–
Follow-up of colonoscopy use after a positive FIT: request reports		–	–	–	–	–	–	–	–	–	✓	–
**Use of colorectal cancer screening in routine practice within 1 year**												
	Use of FITs^f^	–	–	–	–	–	–	–	–	–	–	✓
	Use of colonoscopy^f^	–	–	–	–	–	–	–	–	–	–	✓
	Colonoscopy reports^g^	–	–	–	–	–	–	–	–	–	–	✓

^a^FIT: fecal immunochemical test.

^b^Duration depends on how long insurants are sending back the FITs.

^c^Arm A: invitation + FIT; arm B: invitation + order; and arm C: information only (ie, control).

^d^Not applicable.

^e^Subrandomization in arms A and B: 50% receive reminder.

^f^Aggregated for all arms and additionally pseudonymized for arms A and B where consent was given.

^g^Anonymized for all arms where consent was given.

### Inclusion and Exclusion Criteria

Inclusion criteria for receiving a letter are as follows: (1) aged 50-54 years, (2) enrolled in the AOK Family Doctor Program (HausarztProgramm) of AOK BW (Hausarztzentrierte Versorgung [HZV] contract: § 73b SGB V), and (3) did not receive an invitation in previous rounds of AOK BW model projects in previous years. Exclusion criteria for receiving a letter are as follows: (1) had an insurance-recorded colonoscopy within the past 5 years, (2) had a previous cancer diagnosis, (3) being deceased, and (4) being dependent on care.

Participants with a positive FIT result detected with the provided test kit are contacted by the DKFZ during the second part of the study to follow up on usage and outcome of colonoscopies.

### Part 1: Personal Invitation for Colorectal Cancer Screening

The intervention is a personal invitation letter to perform a commercially available and validated FIT for quantitative detection of human hemoglobin (Hb); the test used is the OC-Sensor FIT (Eiken Chemical, Tokyo, Japan). Study information is being embedded in a mandatory, insurance-related information letter about the offer to undergo colonoscopies from age 50 years, within the AOK Specialist Program. Suitable insured persons are being randomized into three arms—A, B, and C (ie, control)—by AOK BW (randomization was performed using a random number generator: structured query language [SQL] statement, database management system [DBMS]_RANDOM). Letters are being sent out biweekly in six tranches—one-sixth of each arm per tranche. A second randomization is dividing arms A and B into two respective subgroups—arm A: A1 and A2; arm B: B1 and B2. Subgroups A1 and B1 get a reminder letter after 4 weeks. No additional FIT kit is attached to the reminder letter and it states that the reminder is invalid if the FIT offer was already taken or ordered.

Within intervention arm A, insured persons receive a personal invitation letter, which describes CRC screening methods and includes a free FIT in a prepacked test kit. This kit contains one FIT, written and graphical instructions, two stool sample collectors, a record sheet for date of sample taking and year of birth, and a return envelope for mailing the test to the study center at DKFZ. Furthermore, the study information sheet, with optional email or phone consultation by the DKFZ, and the consent form are included.

Within intervention arm B, insured persons are also sent a personal invitation letter describing CRC screening methods, with the additional offer to order a FIT for free from the DKFZ via reply mail, fax, email, or online form. The study information sheet is added, but the consent form is only sent with the prepacked test kit upon FIT request.

Within control arm C, insured persons receive the insurance-related information letter mentioning a colonoscopy but do not receive the FIT itself nor the offer to order a FIT from the DKFZ. They may, however, make use of the FIT in routine practice: aggregated data on routine use is being provided by AOK BW.

Insurants randomized to arms A and B, who decide to take the FIT offer, are asked to sign the informed consent form. By signing this, they agree to the FIT analysis; to receive a written test result, which will also be sent to the family physician if not contradicted; to data storage and evaluation (ie, FIT result, age, gender, and first three digits of postal code); and to be recontacted during follow-up in case of a positive result. Optionally, they can allow the DKFZ to receive pseudonymized claims data from CRC screening participation in routine practice within 1 year after the initial invitation.

As proposed by the FIT manufacturer, participants are being instructed to spread the tip of the test stick over the freshly passed whole feces at various points until the tip’s grooves were filled with feces, and then to reinsert the probe into the device. The serrated probe that is attached to the device cap collects 10 mg feces into 2 mL of buffer. The FIT and the informed consent sheet are mailed to the DKFZ in a postpaid envelope. Upon arrival at the DKFZ, the FITs are stored in a fridge and separated from person-identifying information (ie, pseudonymized). The FITs are then sent by cooled transport to an external certified laboratory: Labor Limbach, Heidelberg, Germany, DIN EN ISO 15189 accredited. Trained laboratory personnel blinded to the randomization arm perform the analysis in a fully automated manner using the original OC-Sensor Pledia FIT device. Samples are disposed of after the analysis. As recommended by the manufacturer, the cutoff for a test result to be positive is 50 ng Hb/mL buffer (equal to 10 µg Hb/g feces). Results above the upper analytical limit of 1000 ng Hb/mL buffer are not diluted and not retested. Collection, arrival, and analysis dates of fecal samples are recorded. The DKFZ receives the laboratory reports, each checked and signed by a certified medical doctor. Additionally, the quantitative test results of the FITs are transferred electronically to the DKFZ, using DocNet plus, version 4 (DocNet Systems GmbH), where they are integrated into the study database.

Missing informed consent forms are being requested before any test analysis starts. Participants with failed tests receive a new test kit (eg, due to failed sampling or if the difference between the day of sample taking and arrival at the DKFZ is more than 7 days without cooling, followed by a negative test result).

The DKFZ sends a notification about the qualitative test result (ie, positive or negative, based on the manufacturer's recommended threshold) to the participants in an understandable manner. With a positive result, a consultation with the general practitioner is recommended to consider a colonoscopy for further examination. A copy of the laboratory report is sent to the family physician, unless participants did not wish so.

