In the randomized substudy, the increase in FIT usage due to a reminder letter in comparison to the one-time invitation will be analyzed. The expected FIT usage in arm A is approximately 40% with the reminder compared to 30% without the reminder; the expected FIT usage in arm B is approximately 20% with the reminder compared to 15% without the reminder. The included sample size of the randomized substudy (ie, 2922 per arm) allows for a precise estimation of the impact of sending a reminder. The expected relative FIT use (95% CI) in subgroups A1 and B1 (ie, received a reminder) compared to the respective subcontrol groups A2 and B2 (ie, one-time invitation only) would be 1.33 (1.24-1.43) and 1.33 (1.19-1.49), respectively. The statistical power to detect an effect of the expected order of magnitude is close to 100%: SAS, version 9.4 (SAS Institute) POWER procedure, two-sided Pearson chi-square test with significance level alpha=.025. For the two comparisons (ie, A1 vs A2 and B1 vs B2), multiple testing was adjusted for, according to the Bonferroni-Holm method. For the most stringent adjustment with alpha=.025 (ie, baseline alpha=.05 with two tests) there is still excellent power.

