### Statistical Analysis

The statistical analysis of this confirmatory study primarily involves comparing the use of FITs in the intervention arms and the control arm within 1 year after the initial letter. In addition, within the intervention arms, the effect of a one-time invitation will be compared to an invitation with a reminder letter.

Comparisons will be done by two-sided chi-square tests for differences in the participation rates. Secondary outcomes will be addressed by descriptive and exploratory analyses. Data for the primary outcome analysis are expected to be complete, as complete information on FITs conducted in routine practice is obtained through insurance claims data (ie, billing codes for laboratory analysis of the FIT), and complete information on FITs conducted through the special offers is directly available from the study center.

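### The reminder comparison (A1 vs A2, B1 vs B2) is unbiased but less precise than the recorded kit dates allow; a supplementary analysis stratified by return before week 4 would narrow its interval

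*Protocol article*

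**What the plan says.** Table 1 of the protocol article places the subrandomisation at T0 and each tranche's reminder four weeks after that tranche's first letter. Its footnote reads "Subrandomization in arms A and B: 50% receive reminder", and Part 1 of the Methods states that "Subgroups A1 and B1 get a reminder letter after 4 weeks". The letter goes to the whole subgroup but carries a disclaimer: "it states that the reminder is invalid if the FIT offer was already taken or ordered".

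For this substudy the Sample Size Calculation section says that "the increase in FIT usage due to a reminder letter in comparison to the one-time invitation will be analyzed". It plans on 2922 persons per subgroup and expects, in arm A, "approximately 40% with the reminder compared to 30% without the reminder"; in arm B it expects 20% against 15%. The resulting ratios are given as 1.33 (1.24–1.43) and 1.33 (1.19–1.49). The Statistical Analysis section says that "the effect of a one-time invitation will be compared to an invitation with a reminder letter" and names two-sided chi-square tests for differences in participation rates.

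For kits sent back to the study center, Part 1 also says: "Collection, arrival, and analysis dates of fecal samples are recorded". Routine-practice FITs are described in Part 2 as totals per study arm and gender, with individual claims data only for participants who gave specific consent.

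**The concern.** Until the reminder goes out, A1 and A2 are treated identically, and so are B1 and B2. A study kit that has reached the study center by that date can be neither caused nor prevented by the reminder. It still counts as an outcome in the planned test, so any chance imbalance in early returns passes straight into the estimated reminder effect.

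Whether a kit had arrived by the tranche's reminder date is a pre-reminder characteristic that allocation cannot influence. It is known for everyone in A and B, because non-return simply counts as no. Stratifying on it preserves the randomised comparison and removes that part of the noise. The protocol justifies the substudy by the precision of its estimate, so an avoidably wide interval is relevant even where power is high.

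**Working it through.** **Inputs from the protocol.** n = 2922 per subgroup; arm A p1 = 0.40, p0 = 0.30; arm B p1 = 0.20, p0 = 0.15; two-sided alpha 0.025 (strictest Holm step).

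**Assumptions.** The share x of invitees whose kit arrived before the reminder is not given. I use 10%, 15%, 20% in arm A and 5%, 7.5%, 10% in arm B. The planned rates are treated as if they were study-kit use.

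**Step 1: reproduce the plan's figures.** SE(log RR) = sqrt[(1−p1)/(n·p1) + (1−p0)/(n·p0)].
- A: sqrt(0.6/1168.8 + 0.7/876.6) = 0.0362, giving 1.33 (1.24–1.43).
- B: sqrt(0.8/584.4 + 0.85/438.3) = 0.0575, giving 1.33 (1.19–1.49).
- Power of the chi-square test at alpha 0.025: above 99.99% (A) and 99.7% (B).

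All agree with the document.

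**Step 2: unadjusted risk difference.** SE = sqrt[(p1(1−p1) + p0(1−p0))/n].
- A: sqrt[(0.24 + 0.21)/2922] = 0.01241; half-width 1.96 × 0.01241 = 2.43 points.
- B: sqrt[(0.16 + 0.1275)/2922] = 0.00992; half-width 1.94 points.

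**Step 3: stratify by early return.** In the early stratum everyone has the outcome, so it contributes a difference of zero and no variance. Among the rest, q = (p−x)/(1−x). The overall adjusted difference is (1−x)(q1−q0) = p1−p0, unchanged at 10 and 5 points. Its SE is (1−x)·sqrt{[q1(1−q1) + q0(1−q0)]/[(1−x)n]}.

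Example, A at x = 0.20: q1 = 0.25, q0 = 0.125, remaining n = 2337.6; SE = 0.8 × sqrt[(0.1875 + 0.1094)/2337.6] = 0.00902; half-width 1.77 points.

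| Arm | Early share x | Half-width, points | Narrower by | Equivalent sample size | Ratio q1/q0 among not yet returned |
|---|---|---|---|---|---|
| A | none used | 2.43 | – | 1.00 | – |
| A | 10% | 2.16 | 11% | 1.27 | 1.50 |
| A | 15% | 1.99 | 18% | 1.50 | 1.67 |
| A | 20% | 1.77 | 27% | 1.89 | 2.00 |
| B | none used | 1.94 | – | 1.00 | – |
| B | 5% | 1.68 | 13% | 1.33 | 1.50 |
| B | 7.5% | 1.53 | 22% | 1.62 | 1.67 |
| B | 10% | 1.34 | 31% | 2.11 | 2.00 |

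**Step 4: does the interval hold?** In simulation (20,000 trials per scenario; A at x = 0.15 and 0.20, B at 0.075 and 0.10, and a null case of 30% vs 30% with x = 0.20) the stratified estimate was unbiased and 95% coverage was close to nominal. The SD fell from about 0.0124 to 0.0090 (A, x = 0.20) and from about 0.0099 to 0.0068 (B, x = 0.10).

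**Step 5: power if the reminder does half as well as planned.**
- A (35% vs 30%): 97% unadjusted; 99.2% to above 99.9% among those not yet returned.
- B (17.5% vs 15%): 64% unadjusted; 79%, 88% or 96% at x = 5%, 7.5% or 10%.

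At the planned effect the chi-square test is already at 99.7% or more, so little is left to gain.

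**The case against.** The strongest reply is that nothing here is wrong. The stated question is total FIT use with and without a reminder, and comparing everyone randomised answers it without bias. The Results section reports 5825 reminders against 2 × 2922 = 5844 planned, or 99.7%, so the policy tested is a blanket reminder, and the planned contrast measures exactly that. A supplementary adjusted analysis is also something an article may leave to an analysis plan that is not shown. All of this stands, except that the article does name the test. A more precise companion analysis can therefore be proposed against it, as an improvement and not as the repair of an omission.

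A reader might infer that 1.33 is a diluted figure and that 1.5 to 2.0 is the true reminder effect. The document does not support this. For total uptake 1.33 is the right ratio; the larger ratios concern people whose kit had not come back by week 4, which is a different question. Nor are they strictly the effect among those the letter addresses. The disclaimer covers offers already taken or ordered, whereas the stratum is defined by return. In arm B it still contains people who had ordered but not yet returned a kit, and the article does not say that order dates are recorded. This costs some precision but causes no bias, because it affects B1 and B2 alike.

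A reader might also infer that the recorded dates remove the noise entirely. They cover study kits only. The planned 40/30% and 20/15% average to 35% and 17.5%, which Figure 1's caption labels total expected use, and participants in A and B can also obtain a FIT in routine practice. Routine FITs are described only as totals per arm and gender, or individually on consent, so the adjustment does not reach them.

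**Conclusion.** The planned reminder comparison is valid and its figures are correct; it is merely less precise than the data allow. With the planned rates read as study-kit use, and with assumed early shares of 10–20% (A) and 5–10% (B), intervals for the risk difference would be 11–27% and 13–31% narrower. The true gain depends on the 4-week return share, which the document does not give, and would be smaller if few kits came back early. This is an inexpensive improvement to a substudy. A reading that the substudy is biased or underpowered as planned is not supported: power changes materially only if the reminder effect falls well below plan, chiefly in arm B. The comparison of arms A, B and C is untouched.

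**What to change.** Keep the planned chi-square comparison of everyone randomised, and add the following for A1 vs A2 and B1 vs B2, for study-kit FITs only:

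1. A risk difference with 95% CI, stratified by whether the kit had arrived by that tranche's reminder date. Apply the same calendar date to A2 and B2, and weight the strata by their pooled shares. If some early kits fail or lack consent, the method still holds; the early stratum then contributes a little variance.
2. As a secondary figure, the risk ratio among those whose kit had not been returned at that date. Label it so, and state that it is not a correction of 1.33 and that in arm B it includes people who had ordered but not yet returned.
3. The number of early returns per subgroup, so that the gain in precision can be seen.

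The cost is a short paragraph of analysis text and a few lines of code on dates already held. Because the article reports data collection and workup as complete, the addition should be labelled supplementary, with the time of its specification stated.
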